### Outcomes

Prespecified outcomes of the effectiveness of the DR pathway and the evaluation of the implementation strategy are tabulated in tables 2 and 3, respectively.

**Table 2 T2:** DR pathway (intervention)-related outcomes

Outcomes	Indicators	Source of data
Clinical effectiveness	Proportion of people screened for DR in each family health centres over 12 months. Proportion of referred patients with STDR. Proportion of ungradable retinal images and percentage of cataract identified from referring these patients. Risk and complication burden in people screened for DR Presenting visual acuity of those referred from the DR pathway compared with those who self-referred to secondary care. Generalisability of the prevalence data compared with house-to-house survey in a neighbouring district.	Data from monthly entries into EHR and study database. −
Safety	Data on complications of the DR pathway	EHR and study database
Cost-effectiveness	The key outcome is the number of cases of severe visual impairment or blindness due to STDR averted as a result of the new DR care pathway and resultant QALY gain. Estimated QALY gain from laser treatment of STDR and from cataract surgery, using utility values from Rachapelle *et al*.^32^ Assumption that the effect of no screening is as in historic studies that reported the rate at which STDR leads to blindness if left untreated.	Data collected in the study, data from the literature and expert opinion where data could not be collected.
Efficiency	Efficiency is defined as optimal use of the service. For this purpose, we will first estimate the time required to process one patient from the path-process analysis. This estimate will be used to determine the number of patients who can be seen on a day. We will then calculate (1−number of patients screened)/number of patients who can be screened). Proportion can be used in a p-type control chart.^33^	Capture efficiencies in structures, resources and processes across the DR care pathway from staff interviews. Path-process mining of patients screened in family health centres analysis will be based on detailed time-event logs of approximately 70 patients from the 16 FHCs
Patient satisfaction	Patients willingness to be screened and their satisfaction with the information provided to them and the care they received	Patient interviews and telephone survey of patients referred to secondary care for treatment

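### The efficiency formula in Table 2 is not a proportion as printed, and its likely intended form is unused capacity with no stated direction

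*Protocol article*

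**What the plan says.** The Efficiency row of Table 2 (protocol article, Outcomes section) sets out the outcome in four steps.

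- Definition: "Efficiency is defined as optimal use of the service".
- Capacity: the time to process one patient comes from the path-process analysis, and "This estimate will be used to determine the number of patients who can be seen on a day". The data-source column says that this "analysis will be based on detailed time-event logs of approximately 70 patients from the 16 FHCs".
- Formula: "We will then calculate (1−number of patients screened)/number of patients who can be screened". A further closing bracket follows in the printed text, so there is one opening bracket and two closing ones.
- Use: "Proportion can be used in a p-type control chart".

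The article gives no numerical capacity or efficiency value. No other section restates the formula, calls the quantity unused capacity, or says whether a high or a low value is good. The Outcomes section presents the contents of Table 2 as prespecified, and the abstract names efficiency among the outcomes other than the primary one.

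**The concern.** The definition, the formula and the intended use do not fit together.

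First, subtracting a patient count from 1 before dividing by capacity gives a negative number on any ordinary clinic day. The row then treats the result as a proportion.

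Second, moving the bracket to the place where it probably belongs repairs the arithmetic but not the meaning. The result is the share of capacity left idle, reported under the name efficiency. Unless told otherwise, a reader who sees a centre with an efficiency of 0.75 will probably take it as well used, when three quarters of its estimated screening capacity went unused.

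What is at stake is the correct computation and reading of one descriptive service measure.

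**Working it through.** **Inputs.** Let *s* be the number screened on a day and *c* the estimated number that could be screened that day. Both are named in the Efficiency row and neither has a value there. I assume *c* = 10, 20 and 40 for illustration. The article states no efficiency figure, so there is nothing to reproduce.

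**Three forms compared.**

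- Printed: (1 − *s*)/*c*
- Likely intended: 1 − *s*/*c*
- Utilisation: *s*/*c*

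With *c* = 20:

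| *s* | (1 − *s*)/*c* | 1 − *s*/*c* | *s*/*c* |
|---|---|---|---|
| 0 | 0.05 | 1.00 | 0.00 |
| 1 | 0.00 | 0.95 | 0.05 |
| 5 | −0.20 | 0.75 | 0.25 |
| 10 | −0.45 | 0.50 | 0.50 |
| 12 | −0.55 | 0.40 | 0.60 |
| 20 | −0.95 | 0.00 | 1.00 |

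For example, at *s* = 12: (1 − 12)/20 = −0.55; 1 − 12/20 = 0.40; 12/20 = 0.60.

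**Does the sign depend on the assumed capacity?** No. For any positive *c*, (1 − *s*)/*c* is above 0 only at *s* = 0, equals 0 at *s* = 1, and is negative from *s* = 2 upward. A fully used day gives (1 − 10)/10 = −0.90, (1 − 20)/20 = −0.95 and (1 − 40)/40 = −0.975.

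**Can the printed form go on a p-chart?** The limits are p̄ ± 3√(p̄(1 − p̄)/*c*). With *s* = 14 and *c* = 20, p̄ = (1 − 14)/20 = −0.65. The variance term is then (−0.65 × 1.65)/20 = −0.0536. It has no square root, so the limits do not exist.

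**Can the likely intended form go on a p-chart?** Yes. With the same *s* = 14 and *c* = 20, p̄ = 1 − 14/20 = 0.30. The limits are 0.30 ± 3√(0.30 × 0.70/20), that is −0.007 to 0.607 before truncation. Utilisation of 0.70 gives 0.393 to 1.007, the exact mirror image. The two charts carry the same information and differ only in direction.

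**Direction.** As *s* rises from 0 to *c*, 1 − *s*/*c* falls from 1 to 0. It is therefore the complement of use, in a row that defines efficiency by use.

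**The case against.** The strongest reply is that this is a typesetting slip and little more. The brackets do not balance, and the next sentence calls the result a proportion, so an analyst would be unlikely to report −0.55. A p-chart often tracks the fraction that falls short, so the leading 1 − may be deliberate, and shortfall from capacity is a legitimate inverse indicator of good use. The row never says that a higher score is better. It also draws on staff interviews and path-process mining, so the outcome does not rest on this ratio alone.

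Most of that stands, and it limits the point. Two things survive it. The formula as printed is wrong and nothing elsewhere in the article corrects it. Once the bracket is moved, the label and the quantity run in opposite directions with no note to the reader.

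A reader might infer more than this, and the article does not support these stronger readings:

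- *No p-chart can be built.* That is true only of the literal expression. The repaired form gives a valid chart on days at or below capacity.
- *Days above estimated capacity are a flaw peculiar to this formula.* If *s* = 1.2*c*, then 1 − *s*/*c* = −0.20 and *s*/*c* = 1.20, so plain utilisation fails as a proportion on such a day too. The article reports no such days, and their handling can be left to the full protocol or analysis plan.
- *Comparisons between centres or months would be reversed.* The row plans no such comparison explicitly, and the source cited for the chart is not available to show which convention was meant.

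**Conclusion.** The point holds as a minor correction. As printed, the efficiency expression is negative for two or more patients screened, whatever the capacity, so it is not a proportion. That conclusion needs no assumption; the assumed capacities only illustrate its size. Reading the intended form as 1 − (screened/capacity) is an inference from the unbalanced brackets and the word proportion. On that reading the measure is sound on days at or below capacity, but it is unused capacity under an efficiency label with no direction given.

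It would be wrong to conclude that the outcome is lost or that the study's results are at risk. Numerator and denominator are both named, so either ratio can be formed. The outcome is secondary and descriptive, and the chart is worded as optional. The primary outcome, the sample size and the regression models do not use this quantity.

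**What to change.** Replace the expression in the Efficiency row of Table 2 with one of the following:

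1. Efficiency = number screened ÷ number who could be screened, with higher values better. This matches the row's own definition directly.
2. Unused capacity = 1 − (number screened ÷ number who could be screened), with the bracket corrected, the measure given that name, and a statement that lower is better.

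The two carry the same information, so the choice is one of presentation. The cost is one line of text, with no new data and no change to any other analysis.

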	Promote adaptability	Identify ways the DR care pathway can be tailored to meet local needs and clarify which elements of the pathway must be maintained to preserve fidelity.
	Provide clinical supervision	The Director of the tertiary centre will provide the overall clinical supervision of the whole DR care pathway. He will also delegate ophthalmologists to provide ongoing supervision for the optometrists involved in grading retinal images.
	Provide local technical assistance	Develop and use a system to deliver technical assistance focused on implementation issues using relevant service providers.
	Purposely re-examine the implementation	Monthly monitoring of screened patients at each family health centre, barriers observed and small changes that are required will be implemented to continuously improve the pathway.
	Remind clinicians	Primary care doctors in family health centres will receive monthly newsletter on the numbers recruited across all centres to highlighting successes and providing potential solutions to issues encountered.
Policy contexts	Issue Government of Kerala approval to enable dilatation of pupils of patients under supervision of family health centres doctors	Ensure doctors at family health centres receive approval for mydriasis in order to deliver the DR care pathway.
	Mandate change	The Health Secretary of State will provide leadership to ensure the prioritisation of the implementation of the DR care pathway.

ASHAs, accredited social health activists; DR, diabetic retinopathy; EHR, electronic health records; GCRF/UKRI, Global Challenge Research Fund/UK Research and Innovation.

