Fidelity	Degree of the DR care pathway implementation. Validation of the DR grading within the telemedicine pathway. Delivery of training and the impact on the DR care pathway.	*Assessment:* Fidelity evaluation in 16 family health centres using a path-process analysis of the screening to identify the common screening pathway across centres. *Data source:* The path-process analysis will be based on detailed time-event logs of 70 patients from the 16 family health centres; a telephone follow-up of referred patients to evaluate uptake of referrals. *Assessment:* Validation of the DR grading will be assessed by the agreement of the DR grade reported by the optometrists at the reading centre in the tertiary centre and those reported by the ophthalmologists in the secondary care centres. *Data sources:* DR grading of referred patients obtained from the reading centre vs secondary care. *Assessment:* Increase in numbers of trained staff per month. *Data sources:* Staff interviews, structured observations and review of facility records. The proportions of doctors trained on laser delivery; data quality on the database; increase in non-communicable diseases registration following start of programme due to training of ASHA workers on diabetes and DR; increase in numbers of patients treated for STDR following training.
Penetration	Increase patient awareness of diabetes and DR and uptake of the DR screening pathway in patients with diabetes.	*Assessment:* Increase uptake of DR screening by patients registered in non-communicable diseases registers. *Data sources:* from non-communicable diseases register and EHR.
Sustainability	Policy makers to prepare policy on up-scale and sustainability plan for DR pathway. Integration of DR pathway in weekly activities in FHCs	*Assessment:* Availability of a policy paper from Government of Kerala on state-wide scale up of the DR care pathway. This will be considered a success of the programme. *Data sources:* Scale up plan for other districts including plan to purchase retinal cameras and acceptance of guidelines and training material for state-wide roll out. *Assessment:* Integration of DR pathway in EHR. *Data source:* EHR records of DR screening as part of non-communicable diseases care pathway.

ASHA, accredited social health activists; DR, diabetic retinopathy; EHR, electronic health records; FHCs, family health centres; STDR, sight-threatening diabetic retinopathy.

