### Statistical analyses

We will create a complete case data set of the cross-sectional survey for use in the analyses of effectiveness and assess the potential impact of missing data using sensitivity analysis incorporating a range of optimistic and pessimistic scenarios for the impact of missing data. We will model two outcomes that we hypothesised would be influenced by the intervention: (1) uptake of DR screening (primary outcome) and (2) numbers of patients referred for STDR as a result of screening. We will use bivariate logistic regression models to assess crude associations between sociodemographic factors such as age, gender, education, income and living arrangements, and other clinical data with DR and STDR and use fractional polynomials to account for the form of continuous covariates to predict uptake of DR screening. Factors associated with a p<0.25 will be candidates for inclusion in the multivariable logistic regression models. We will test interactions among identified main effects to capture improvement in model prediction assessed by reduced residual variance-based statistics. To account for the staggered entry into the study, we will add a variable indicating the month of entry of each FHCs into the programme (eg, 1. if the FHC join in the first month of the programme, 2. if in the second month and so on). A non-significant coefficient for this variable will suggest the staggered approach had no effect and a significant coefficient will allow the effect to be quantified for each FHC. In our final adjusted model, we will consider associations with a p<0.05 as statistically significant. Adequacy of model discrimination and calibration will be assessed using receiver operating characteristic curves. The validation of the telemedicine will be reported as the agreement (kappa statistics) between screen positive patients graded by the graders at the reading centre versus the DR grade as recorded by the ophthalmologists in secondary care centres. A kappa coefficient of 0.6 or higher was prespecified to indicate validity.

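### Table 3's first fidelity indicator is assessed by finding the pathway that centres share, with no stated comparison with the intended pathway, so a core screening step omitted widely could go undetected

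*Protocol article*

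**What the plan says.** The Fidelity row of Table 3 in the protocol article lists three indicators.

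- The first is "Degree of the DR care pathway implementation". Its assessment is "Fidelity evaluation in 16 family health centres using a path-process analysis of the screening to identify the common screening pathway across centres". The data are described as follows: "The path-process analysis will be based on detailed time-event logs of 70 patients from the 16 family health centres; a telephone follow-up of referred patients", the follow-up serving to measure uptake of referrals.
- The second concerns grading: "Validation of the DR grading will be assessed by the agreement of the DR grade reported by the optometrists at the reading centre", set against the grade recorded by ophthalmologists in secondary care. The Statistical analyses section adds a benchmark: "A kappa coefficient of 0.6 or higher was prespecified to indicate validity".
- The third concerns training, assessed by "Increase in numbers of trained staff per month", with interviews, structured observations and facility records as sources.

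Elsewhere the article supplies what could serve as a reference. The section on the evidence-based clinical intervention lists the components of the pathway and points to Figure 1. Table 1 plans an implementation blueprint and, under promoting adaptability, undertakes to "clarify which elements of the pathway must be maintained to preserve fidelity". The Sample size section also says that the primary outcome reflects fidelity.

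**The concern.** Degree of implementation compares what was delivered with what was intended. A common pathway compares what was delivered in one place with what was delivered in another. The two agree only when the shared practice is also the planned practice, and that is what a fidelity assessment is meant to find out.

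The distinction matters in a type 2 hybrid study, which evaluates the clinical pathway and its implementation together. If uptake or image quality disappoints, the reader needs to know whether the pathway was delivered as planned and fell short, or was not delivered as planned. The results are also meant to inform state-wide scale-up, and an omission shared by the pilot centres could be carried forward unnoticed.

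The article describes routes by which centres could be affected together. Image capture is taught partly by a train-the-trainer cascade, and pupil dilatation at the centres depends on a government approval. This makes a shared omission possible. The documents do not show that it is likely.

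**Working it through.** The article gives no figure to reproduce here. The check sets the parts of the plan side by side and adds one small illustration.

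**Step 1. Indicator, assessment and yardstick, from the Fidelity row and the Statistical analyses section**

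| Indicator | Assessment | Stated yardstick |
|---|---|---|
| Degree of implementation | Path-process analysis to find the common pathway; telephone follow-up on referrals | None |
| Validity of grading | Reading-centre grade against secondary-care grade | Kappa of 0.6 or higher |
| Delivery of training | Monthly growth in trained staff | None; counts staff |

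Only the first assessment looks at the steps of the screening visit, and no reference is given for it. The intended pathway, the blueprint and the promised core elements all appear elsewhere in the article, but the row refers to none of them.

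**Step 2. Illustration, with assumed numbers**

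The text does not count the steps of the visit, and Figure 1 was not available in the text read, so the number of steps is assumed. Let the intended visit have k steps, and let all 16 centres omit the same one.

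- The common pathway contains k − 1 steps, and every centre delivers all of them. Agreement with the common pathway = (k − 1)/(k − 1) = 100%.
- Adherence to the intended pathway = (k − 1)/k.

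| k | Agreement with common pathway | Adherence to intended pathway |
|---|---|---|
| 4 | 100% | 75% |
| 5 | 100% | 80% |
| 10 | 100% | 90% |

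Agreement with the common pathway stays at 100% for any k, so it carries no information about the omission. If the step is omitted in most centres only, it still drops out of the common pathway, whether common means the most frequent route or the steps shared by all. The logs would then show variation, but nothing stated says which variant departs from the plan.

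**Step 3. Would another measure reveal the omission?**

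- *Grading agreement* concerns screen-positive, referred patients. It tests the reading of images and says little about the steps of the visit.
- *Training counts* measure inputs. Structured observations are listed only as a source for the training assessment.
- *Telephone follow-up* measures what happens after referral.
- *Ungradable images* (Table 2, with continuous monitoring in Table 1) could signal a problem, but the article itself expects cataract to raise this proportion, so the cause would be unclear.
- *Proportion screened, monthly monitoring per centre, reasons for non-referral and numbers denied screening* count patients or record events around the visit. They do not show which steps a screened patient received.

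Some under-delivery could surface through these sources. None clearly isolates a step missing inside the visit.

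**Step 4. What the logs can support**

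70 / 16 = 4.4 logs per centre on average. A pooled summary therefore suits these data, and the fix uses one.

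**The case against.** The strongest reply is that the article does not exclude a comparison with the intended pathway. Detailed time-event logs record what happened, and describing the observed route is a natural first step before setting it beside Figure 1. A journal article may leave that step to a fuller document, and the core elements are still to be clarified. This has weight, but it does not dispose of the point. The row does state a purpose for the analysis, and that purpose does not match the indicator beside it. A fuller document would have to change the stated aim as well as add detail.

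Three stronger readings are tempting and are not supported.

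- A reader might infer that the plan would rate a step omitted everywhere as full fidelity, or would mark centres that follow the planned pathway as deviant. The article defines no score, no reference and no such labels. It supports only the statement that the analysis could not, by itself, detect the omission.
- A reader might infer that the whole fidelity evaluation rests on similarity between centres. It is one of three assessments in the row, and the other two do not rest on similarity.
- A reader might object that about four logs per centre are too few for centre-level conclusions. The article promises no per-centre fidelity estimate from the logs, so this would criticise an analysis that nobody has planned.

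The objection also fairly notes that training includes several sessions at each centre and hands-on teaching by camera manufacturers, and that no stated decision threshold depends on the path-process result.

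**Conclusion.** The point holds for the first fidelity indicator. Its stated assessment describes consistency between centres and names no comparison with the intended pathway. Followed as written, it could not by itself reveal a core step of the screening visit that is omitted or altered in most or all centres, and the other planned measures do not clearly fill that gap.

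The size cannot be estimated from the documents. The illustrated gap (100% against 75% to 90%) rests on an assumed number of steps and on one omission shared by all centres, and it shows the mechanism only. Neither the primary outcome nor the sample size is affected. The change is worth making because it bears on how the effectiveness results are interpreted and on what is scaled up.

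**What to change.** Reword the first assessment in the Fidelity row and add a checklist:

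1. Keep the time-event logs as planned ("The path-process analysis will be based on detailed time-event logs of 70 patients from the 16 family health centres"). Compare each log with the intended pathway, as set out in the intervention section, Figure 1 and the blueprint, and with the core elements that Table 1 says will be clarified.
2. Have the sponsor fix those core elements before the logs are analysed, so that observed practice does not define its own standard. Which elements are core is the sponsor's decision.
3. Report the percentage of core elements delivered, pooled over the logs.
4. Where a step is already recorded for all screened patients, report delivery from those records. The Data collection section gives examples, such as the retinopathy grade in both eyes and image gradability.
5. Present the common pathway as a description of process, where it also serves the efficiency and timeliness outcomes in Table 2, and not as the measure of fidelity.

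No extra patients or visits are needed. The cost is a checklist, a small additional analysis of data already planned, and the possibility that reported fidelity will be lower than agreement with the common pathway would suggest.
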